**Fig. 1 Fig1:**
[figure not shown]
Study calendar

### Study endpoints

The primary endpoint is the 2-year RFS rate. Secondary endpoints include operative time, intraoperative blood loss volume, and transfusion; incidence of postoperative complications within 90 days after surgery (including grade B or C pancreatic fistula, delayed gastric emptying (DGE), and intra-abdominal hemorrhage); all-morbidity rate within 90 days after surgery; and mortality rate within 90 days after surgery. We also include the rates of R0 and R1, number of harvested lymph nodes, number of metastatic lymph nodes, lymph node ratio, overall survival (OS) time, RFS time, and local recurrence rate. R0 status is defined as the absence of tumor cell infiltration within 1 mm of the resection margin, and R1 status is defined as the presence of tumor cell infiltration within 1 mm of the resection margin [13]. Postoperative pancreatic fistula (POPF) [14], DGE [15], and intra-abdominal hemorrhage [16] are defined and graded according to the International Study Group of Pancreatic Surgery (ISGPS) criteria. Postoperative complications other than POPF, DGE, and intra-abdominal hemorrhage are graded by the Clavien-Dindo classification [17]. Postoperative diarrhea is graded according to the Common Terminology Criteria for Adverse Events version 4.

### Statistical analysis

#### Sample size

Clinical trials of isolation and conventional procedures during distal pancreatectomy for pancreatic body/tail cancer have not been widely reported. A two parallel multicenter randomized selection phase II trial compared the conventional procedure with isolation procedure as a basis for a future phase III trial [18]. Its principal aim was to evaluate whether the isolation procedure has a better 2-year recurrence-free survival rate than the conventional procedure in DPS for PDAC. In an observational study, Abe et al. reported that the recurrence rate during the approximately 2-year follow-up period of the conventional procedure was 75%, whereas that of the isolation procedure was 67% [7]. In the current study, we also assume that each group will have a similar 2-year progression-free survival rate. We therefore calculated the number of patients required on the basis of a selection design so that the conventional procedure arm would select a regimen with a 2-year recurrence-free survival rate 8% higher than the expected value with 80% probability. The minimum required number of cases is 46 cases per group. Assuming that approximately 10% of ineligible cases will occur, the target number of registered cases is set to 50 per group (100 cases in total).

#### Statistical analysis plan

The primary population for efficacy analysis will be the intention-to-treat population, defined as all randomized patients. The primary endpoint is the 2-year RFS rate. The primary analysis will be based on the full analysis set (FAS), which consists of all randomized patients except those found to be ineligible after enrollment. The Kaplan-Meier method will be used to estimate the progression-free survival curve and 2-year progression-free survival rate. The regimen with a higher 2-year progression-free survival rate will be considered as the more promising procedure of the two. The Brookmeyer-Crowley method will be used to calculate the 95% confidence interval for the 2-year progression-free survival rate. Although the design of choice cannot confirm the results based on a hypothetical test, it would compare the progression-free survival curves using the log-rank test as a reference. A Cox proportional hazard model will be applied to calculate HRs and 95% confidence intervals adjusted for stratification factors (i.e., approach method and preoperative adjuvant therapy). For evaluation of secondary endpoints, categorical outcomes will be summarized using frequency and percentage for each arm and will be compared using Fisher’s exact test. Mann-Whitney-Wilcoxon test will be used to compare continuous outcomes and will be summarized using the median and interquartile range.

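### The confidence interval for the 2-year recurrence-free survival rate is assigned to Brookmeyer-Crowley, a method that gives an interval for a survival time and not for a rate

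*Protocol article*

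**What the plan says.** The Study endpoints section of the protocol article states: "The primary endpoint is the 2-year RFS rate". The Statistical analysis plan section repeats this and names the estimator: "The Kaplan-Meier method will be used to estimate the progression-free survival curve and 2-year progression-free survival rate". It then names the interval: "The Brookmeyer-Crowley method will be used to calculate the 95% confidence interval for the 2-year progression-free survival rate".

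The decision rule in the same section uses only the point estimates: "The regimen with a higher 2-year progression-free survival rate will be considered as the more promising procedure of the two". The section adds that a selection design does not confirm results by a hypothesis test. A log-rank test is planned for reference only, and Cox hazard ratios with 95% confidence intervals are adjusted for the stratification factors.

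No other interval method for the 2-year rate appears in the article. The secondary endpoints include overall survival time and RFS time, but no median is named to which Brookmeyer-Crowley might have been meant to apply.

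**The concern.** Brookmeyer-Crowley inverts a test of whether survival at time *t* equals a fixed probability, and collects the values of *t* that are not rejected. The result is an interval in units of time for a quantile, usually the median. The primary endpoint runs the other way: the time is fixed at 24 months and the probability is unknown. Setting the method to a quantile other than the median does not help, because the answer is still in months.

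The selection rule calls the arm with the higher rate more promising however small the gap, and no confirmatory test stands behind it. The reader therefore depends on the interval to see how uncertain each 2-year rate is. Followed literally, the plan leads to a range of months presented as the interval for a rate, or to no interval for the rate at all. If the analysts quietly substitute another method, that method was not prespecified. The Sample size section describes the result as a basis for a future phase III trial, so the precision of these rates will be read closely.

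**Working it through.** **Inputs**

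- Planning rates (Sample size section): recurrence over about 2 years with "the conventional procedure was 75%, whereas that of the isolation procedure was 67" percent. The 2-year RFS rates are therefore 1 − 0.75 = 0.25 and 1 − 0.67 = 0.33.
- Selection target (same section): a "2-year recurrence-free survival rate 8% higher than the expected value with 80% probability".
- Size (same section): "The minimum required number of cases is 46 cases per group".
- Assumptions made here, not in the article: no censoring before 24 months and, for the medians only, exponential RFS.

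**Step 1. Reproduce the plan's own figure.** For a pick-the-winner design,

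n = z(0.80)² × [p₁(1 − p₁) + p₂(1 − p₂)] / (p₂ − p₁)²

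= 0.8416² × (0.1875 + 0.2211) / 0.08² = 45.2, rounded up to 46 per group.

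The exact binomial probability of correct selection at 46 per group, with ties split evenly, is 0.801. The stated 46 is reproduced, which confirms that the trial was planned on a proportion at 2 years.

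**Step 2. The interval the endpoint needs.** Without censoring, Greenwood's standard error is SE = √[p(1 − p)/n]. The log-log limits are p^exp(±1.96 × SE / (p × |ln p|)).

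- p = 0.25, n = 46: SE = √(0.1875/46) = 0.0638. The exponent term is 1.96 × 0.0638 / (0.25 × 1.386) = 0.361. The limits are 0.25^1.435 = 0.137 and 0.25^0.697 = 0.381.
- p = 0.33, n = 46: SE = √(0.2211/46) = 0.0693. The exponent term is 1.96 × 0.0693 / (0.33 × 1.109) = 0.371. The limits are 0.33^1.450 = 0.200 and 0.33^0.690 = 0.465.

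**Step 3. What Brookmeyer-Crowley returns on the same curves.** Under exponential RFS the median is 24 × ln 2 / |ln p|, which is 12.0 months for p = 0.25 and 15.0 months for p = 0.33. Place 46 event times at the (i − 0.5)/46 quantiles and keep every step of the curve with |S(t) − 0.5| ≤ 1.96 × SE. The steps from S = 29/46 to S = 17/46 are kept, that is, from the 17th event time to the 30th.

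| 2-year RFS rate | Greenwood, log-log | Greenwood, plain | Brookmeyer-Crowley (median) |
|---|---|---|---|
| 25% | 13.7% to 38.1% | 12.5% to 37.5% | 7.7 to 17.8 months (12.0) |
| 33% | 20.0% to 46.5% | 19.4% to 46.6% | 9.6 to 22.2 months (15.0) |

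The last column answers a different question in different units. With 50 patients per arm the log-log intervals are 14.1% to 37.5% and 20.5% to 46.0%, so the picture does not depend on how many patients prove ineligible.

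**The case against.** The strongest reply is that little turns on this interval. The chosen arm depends on two Kaplan-Meier estimates alone. The 46 per group rests on a probability of correct selection, with no interval and no alpha. An interval in months beside a percentage would look wrong at once, and a competent statistician would take the pointwise interval from the same Kaplan-Meier fit. The Cox model also supplies a valid interval for a comparison of the arms. On this reading the defect is a wrong method name attached to a descriptive quantity.

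The first part stands: neither the selection nor the sample size is affected, and no bias in the result is shown. The figures above show the scale of the correct interval, not an error in the trial's conclusion.

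The rest does not remove the point. A hazard ratio and a log-rank test describe the whole curves and not the rate at 24 months, so the misassigned interval is the only one planned for the primary endpoint itself. That the error would probably be noticed at analysis is a reason to correct it beforehand, so that the method actually used is prespecified. Nor can the sentence be excused as detail left to a fuller document, since it names both a method and a target and the two do not match.

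It is also fair to say that the log-log scale is a choice. The plain Greenwood limits are close, and either would be acceptable if named. An interval for the between-arm difference goes beyond the defect, though it is useful here.

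**Conclusion.** The concern holds. As written, the confidence interval for the primary endpoint cannot be produced by the method assigned to it, and nothing else in the article corrects this. The intervals that should be reported are wide: at the planning rates they overlap from 20.0% to 38.1%, which is the uncertainty a reader must see beside a label of more promising. These figures assume 46 patients per arm and no censoring before 24 months. The median times used for contrast also assume exponential RFS. The mismatch between method and endpoint depends on none of these assumptions. The harm is confined to the reporting and prespecification of the primary result.

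**What to change.** Replace the sentence in the Statistical analysis plan section with wording such as: *The 95% confidence interval for the 2-year RFS rate in each arm will be a pointwise Kaplan-Meier interval using Greenwood's variance with the complementary log-log transformation. The between-arm difference in 2-year Kaplan-Meier rates will be given with its 95% confidence interval.* The first sentence is the necessary correction, and the second is a recommended addition. Keep Brookmeyer-Crowley only for median RFS and median overall survival, if these are reported.

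The same edit should change progression-free to recurrence-free survival in this section, so that the analysis names the endpoint as defined.

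The cost is one sentence in the protocol and SAP, made before the analysis. Pointwise intervals are a standard option in survival software. Design, sample size, data collection and patient care are unchanged.

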#### Study population

Table 1 shows a detailed overview of all eligibility criteria. Patients are eligible if they meet the ISOP-DP trial definitions for resectable PDAC and no contact with the portal vein (PV) and superior mesenteric vein (SMV), and are scheduled to undergo DPS. Resectable PDAC is defined according to the *Classification of Pancreatic Carcinoma of Japan Pancreas Society (Fourth English Edition)* [19] and the National Comprehensive Cancer Network (NCCN) definition 2020 [20]. Patients eligible for inclusion in this study are those undergoing open or laparoscopic DPS for pancreatic body and tail cancer after excluding those with intra-ductal papillary mucinous neoplasm, neuroendocrine tumors, mucinous cystic neoplasm, or metastatic pancreatic tumors or similar. In addition, simultaneous resection of the pancreatic parenchyma and splenic vein in one session will be rendered possible through evaluation of preoperative imaging study findings. Patients indicated for spleen-preserving distal pancreatectomy (SPDP) and those indicated for the Warshaw operation (spleen-preserving and splenic artery/vein resection) will be excluded.

**Table 1 Tab1:** Eligibility criteria

Inclusion criteria	Exclusion criteria
(1) Patients who have been diagnosed with resectable pancreatic cancer (adenocarcinoma, adenosquamous cell carcinoma, mucinous carcinoma, and anaplastic carcinoma) according to the *Classification of Pancreatic Carcinoma of Japan Pancreas Society (Fourth English Edition)* [18] and the *National Comprehensive Cancer Network (NCCN) definition 2020* [19], excluding invasive intraductal papillary mucinous carcinoma (IPMC) by image diagnosis at the initial diagnosis, and for whom body-tail pancreatectomy or tail pancreatectomy is planned. Preoperative biopsy is not mandatory, however, and allows clinical diagnosis. (2) ASA-PS (American Society of Anesthesiology, General condition classification) is Class 1–3. (3) Age over 20 years. (4) Patient has sufficient judgment to understand the content of the research and has provided written consent.	(1) Patients who have not been diagnosed with resectable pancreatic cancer by image diagnosis as the initial diagnosis. (2) Patients with tumor suspected of portal vein (superior mesenteric vein) invasion. (3) Patients with severe ischemic heart disease. (4) Patients with cirrhosis or active hepatitis requiring treatment. (5) Patients with dyspnea requiring oxygen administration. (6) Patients undergoing dialysis due to chronic renal failure. (7) Patients with tumor for which arterial reconstruction of the superior mesenteric artery, common hepatic artery, celiac artery, etc. is considered necessary. (8) Patients with strong suspicion of paraaortic lymph node metastasis. (9) Patients with active double cancer thought to affect adverse events and prognosis. (10) Patients with usage of long-term oral steroids that may affect adverse events. (11) Patients considered to have potential difficulty participating in the study due to psychosis or psychiatric symptoms. (12) Cases other than invasive pancreatic ductal carcinoma by preoperative biopsy. Invasive pancreatic ductal carcinoma is classified into four types: adenocarcinoma, adenosquamous cell carcinoma, mucinous carcinoma, and anaplastic carcinoma, and invasive intraductal papillary mucinous carcinoma (IPMC) is excluded. However, a preoperative biopsy is not mandatory. (13) Patients who cannot use either iodine and gadolinium contrast agent due to severe drug allergy. (14) Patients whose abdomen makes it difficult to perform the prescribed procedure due to a history of upper abdominal surgery, such as on the stomach, spleen, kidney, liver, transverse colon, or retroperitoneum, including the pancreas and for pancreatitis. (15) Patients who may require resection of organs other than the spleen, left adrenal gland, and gallbladder.

*Abbreviations*: *ASA-PS* American Society of Anesthesiologists-Physical Status

### Randomization

After confirmation of eligibility including written informed consent, patients will be randomized in a 1:1 allocation ratio to either arm A (conventional approach) or arm B (isolation approach) with a random block size. Central randomization and registration will be applied, using UMIN Internet Data and Information system for Clinical and Epidemiological research, cloud version (INDICE cloud). After assessment for eligibility at registration, patients will be centrally randomized to either arm A or arm B. To minimize background bias between the two groups, this study is stratified by participating institution according to use of minimally invasive approach (yes or no), and preoperative adjuvant therapy (yes or no). The indication and regimen for preoperative adjuvant therapies depend on the treatment strategies of the participating institutions. We use Pocock and Simon’s minimization method for random assignment and the Mersenne Twister for random number generation (Fig. 2, flow diagram of the ISOP-DP trial). All patients are blinded to the surgical approach they will receive, and they are required to sign an informed consent form before enrollment in the study. Blinding of the surgeons is not possible because of the different techniques used during the operation. Assessment of the result will be made by one of two independent researchers ([name], [name]) who will be blinded to the surgical procedures. Once distal pancreatectomy is performed, there is no difference in postoperative radiographic findings between the two surgical approaches, so it should not affect the radiologist’s assessment.

**Fig. 2 Fig2:**
[figure not shown]
Flow diagram of the ISOP-DP (isolation procedure vs. conventional procedure during distal pancreatectomy) trial

### Interventions

#### Trial intervention (isolation approach)

In the isolation procedure group, transection of the root of the splenic artery (SA) and the pancreatic transection are performed first, followed by division of the splenic vein (mandatory procedure). At that time, the branch from the splenic artery (dorsal pancreatic artery), the branch to the splenic vein (left gastric vein, inferior mesenteric vein), and the short gastric artery and vein are also disconnected as soon as possible (recommended procedure). An operation to lift up the pancreatic neck from the dorsal portal vein or superior mesenteric artery to expose the splenic vein (so-called tunneling) is allowed. After that, lymph node dissection, such as of hepatoduodenal mesentery (lymph node No.12) [19], and around the common hepatic artery perimeter (lymph node No.8) [19], and lymph node dissection around the SMA (lymph node No.14p) [19] are performed (recommended procedure). At the end of the resection operation, the pancreatic body/tail and the spleen are mobilized and removed (required procedure) by detachment of the retroperitoneum. Strasberg et al. described the division of the left gastric artery as an optional step that may be omitted; otherwise, this procedure is identical to the RAMPS procedure [5].

#### Control intervention (conventional approach)

In the conventional procedure group, first, the pancreatic body and tail and spleen are mobilized by detachment of the retroperitoneum (mandatory procedure). The regional lymph nodes of the pancreatic body/tail, such as the hepatoduodenal mesentery (lymph node No. 12) [19] and the common hepatic artery perimeter (lymph node No. 8) [19], are removed (recommended procedure) and dissection of lymph nodes (lymph node No.14p) [19] around the SMA (recommended procedure). After dissection of the gastro-splenic ligament and pancreatic transection, the splenic vein is divided at the end of the resection procedure (required procedure), although pancreatotomy or division of the SA in early phases is allowed to prevent bleeding and secure a safe field of view.

#### Common to both groups (allowable procedure)

In both groups, the spleen is resected with the pancreas. The direction of the detachment of the pancreatic body/tail from the retroperitoneum is recommended to proceed from the right side to the left side. Lymph node dissection shall be regional lymph node dissection (lymph node Nos. 8a, 8p, 12a, 12p, 11p, 11d, and 14p) in the *Classification of Pancreatic Carcinoma of Japan Pancreas Society (Fourth English Edition)* [19] (recommended procedure). As a general rule, the nerve plexus around the SMA is preserved all around (recommended procedure).In both groups, the approach of open surgery, laparoscopic surgery, and robotic surgery is left open to the decision of the operators.To ensure safety, conversion from laparoscopic or robotic surgery to open surgery based on the intraoperative findings such as uncontrollable bleeding or severe adhesion is acceptable. However, the conversion from open surgery to laparoscopic or robotic surgery is not specified.For safety, with consideration of bleeding prevention, it is permissible to perform adhesion detachment around the spleen.Hemostasis (compression, suturing, branch transection) is permissible if there is bleeding from portal veins.The method of pancreatic transection or the method of closing the pancreatic stump is left open to the decision of the operators.Splenic vein resection together with the pancreatic parenchyma after isolation of the parenchyma during DPS is acceptable if it can be safely performed.Combined resection of the surrounding organs other than the spleen (stomach, large intestine, etc.) is allowable. However, if the surgical procedure is changed to portal vein resection, celiac artery resection, exploratory laparotomy, etc. during the operation, it will be considered as a deviation, and the protocol treatment will be stopped according to the criteria for discontinuing protocol treatment. Patients with protocol deviation must be followed in an intention-to-treat analysis.If essential procedures cannot be performed in either group, it is considered to be a deviation and the protocol treatment is stopped according to the criteria for discontinuing protocol treatment. Whether or not the recommended procedure is performed is not treated as a target of deviation judgment.

### Standardization and validation of interventions

To guarantee the quality of both procedures, board-certified surgeons from the Japanese Society of Hepato-Biliary-Pancreatic Surgery perform or supervise all surgery. Both procedures are performed in daily practice depending on the case. Before the start of the ISOP-DP trial, all participating surgeons in this trial held consensus meetings to determine the details of the operative techniques for both groups by observing and discussing several operative videos to ensure standardization of the interventions in all institutions at which more than 50 pancreatectomies for pancreatic cancer were performed per year, in accordance with the Japanese Pancreatic Cancer Treatment Guidelines. On the basis of the meetings, we determined that a photographic record after pancreatic transection is necessary for both groups for validation of intervention quality, because the operative techniques of this approach have been certified by the Japanese Society of Hepato-Biliary-Pancreatic Surgery. Central judgment will be conducted for both groups, and the intraoperative images are evaluated to determine whether the procedure is performed according to the protocol by three reviewers (two independent surgeons and principal investigator); cases with discrepancies are re-evaluated simultaneously by the three reviewers until a consensus is reached. If there is disagreement among the three reviewers, the majority classification is chosen to settle whether the procedure has been performed according to the protocol. If it is determined that the procedure is not performed according to the protocol, it will be treated as a case that deviates from the protocol.

### Recruitment

To achieve adequate participant enrollment to reach the target sample size within the study period, 11 Japanese high-volume centers will participate in the ISOP-DP trial.

